#### Randomization

Randomization is computerized using a minimization strategy while stratifying over the following variables: a) research centre, b) full versus partial remission (IDS-C score ≤ 11 versus > 11), c) number of depressive episodes in the past (3-4 versus ≥ 5), d) prior CBT (yes/no) and e) gender. Sub–threshold symptoms (partial remission) and number of past episodes are stratified because both are associated with relapse/recurrence risk [55]. Also, prior CBT is stratified because this has been shown to decrease relapse/recurrence risk [56]. Randomization is performed online by the research assistant who conducts the baseline assessment by entering the required information on a randomization website specifically designed for this study. The research assistant then communicates the treatment allocation to the patient, which means that he or she is no longer blind to the treatment condition. Unblinding of patients and research-assistants could not be avoided because the different conditions required different arrangements for treatment appointments, and separating this task from the assessments was logistically impossible in most research centers. To assess the reliability of the follow-up assessments, all interviews are audio taped and a random selection of actual, borderline or probable cases of relapse/recurrence is rated by an independent assistant blind to treatment allocation.

#### Follow-up assessments

In accordance with previous trials [19,20,23], follow-up assessments take place at 3, 6, 9, 12 and 15 months post randomization (Table 1). The follow-up assessments at T2, T3 and T4 are administered by telephone and consist of only an interview part. If participants miss one or more assessments, research assistants examine the entire period from the last contact. In case of drop-out, we send a short questionnaire to gather essential information about depressive relapse/recurrence (if applicable) and the main reason for drop-out.

### Statistical analysis

#### Primary analyses

Our primary analyses will be based on intention-to-treat. Subsequently per-protocol analyses will be conducted. All analyses will be performed with and without covariates (i.e. the stratification factors research centre, depressive symptoms at baseline, and number of depressive episodes in the past, as well as other variables that might inadvertently be unevenly distributed over the conditions at baseline). *Trial 1: mADM* versus *mADM + MBCT.* The primary outcome measure will be relapse and/or recurrence meeting DSM-IV criteria for a major depressive episode during the 15-month study period. Relapse/recurrence rates will be compared with a Chi-square test. *Trial 2: MBCT* versus *mADM + MBCT.* The primary outcome measure will be relapse and/or recurrence meeting DSM-IV criteria for a major depressive episode during the 15-month study period. Relapse/recurrence rates will be compared with a General Linear Model using a binomial family with an identity link. We will use the confidence interval (one-sided) of the difference in relapse/recurrence between the two conditions (MBCT versus mADM + MBCT): if a difference of 25% can be excluded, then we will conclude non-inferiority of MBCT in comparison with mADM.

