## Abstract

**Background:**

Depression is a common psychiatric disorder characterized by a high rate of relapse and recurrence. The most commonly used strategy to prevent relapse/recurrence is maintenance treatment with antidepressant medication (mADM). Recently, it has been shown that Mindfulness-Based Cognitive Therapy (MBCT) is at least as effective as mADM in reducing the relapse/recurrence risk. However, it is not yet known whether combination treatment of MBCT and mADM is more effective than either of these treatments alone. Given the fact that most patients have a preference for either mADM or for MBCT, the aim of the present study is to answer the following questions. First, what is the effectiveness of MBCT in addition to mADM? Second, how large is the risk of relapse/recurrence in patients withdrawing from mADM after participating in MBCT, compared to those who continue to use mADM after MBCT?

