### Sample size

#### *Trial 1: mADM* versus *mADM + MBCT*

For trial 1 we need to recruit 96 participants (n = 48 per group) in order to demonstrate a difference of 25% in relapse/recurrence rates between mADM and mADM + MBCT, with a power of 80% (alpha 0.05, one-sided). This calculation is based on earlier studies reporting relapse/recurrence percentages of 60% in the mADM group [23] and approximately 38% in the MBCT plus TAU group [25]. Because our trial investigates MBCT plus mADM rather than MBCT plus TAU, we expect an even lower relapse/recurrence percentage (about 35%) in the combination group. Our expected difference is therefore 60% (mADM) minus 35% (mADM + MBCT) resulting in 25%.

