#### *Trial 2: MBCT* versus *mADM + MBCT*

The sample size of trial 2 is based on the principle of non-inferiority. According to the Draft Guidance for Industry Non-Inferiority Clinical Trials of the US Food and Drug Administration [26] non-inferiority should be demonstrated by comparing the new, experimental treatment with an established efficacious treatment. In the case of relapse prevention in depression, this established treatment is mADM. However, since a head to head comparison of MBCT with mADM is complicated due to our design, we compare MBCT with the combination therapy (mADM + MBCT). We reasoned that the difference in relapse/recurrence between MBCT and mADM + MBCT should not be larger than the difference between the established treatment (mADM) and mADM + MBCT, which is expected to be approximately 25%. Therefore, we chose a non-inferiority margin of 25%. Based on this assumption, the sample size needed in this non-inferiority trial is 280 in total (n = 140 per group) with a power of 80% (alpha 0.05, one-sided).

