#### *MBCT (with tapering of mADM*)

In the ‘MBCT only’ condition participants are invited to take part in the MBCT course as described above. In addition, they are asked to taper off their mADM from session 7 of the MBCT course onwards. The protocol specifies a tapering scheme lasting 5 weeks for all common ADMs, especially addressing procedures to handle symptoms characteristic for discontinuation [37] (available on request). In case of more exceptional treatments (e.g. lithium addition) withdrawal is based on the shared opinion of the authors of the medication protocol. Clients are seen by a consultant psychiatrist for a minimum of 3 and a maximum of 12 appointments. The first three consultations are scheduled around session 1 (informing and preparing participants), session 7 (initiating withdrawal) and approximately four weeks after session 7 (evaluation of withdrawal). If more guidance is needed, additional appointments can be scheduled. Patients are reassured that they can restart ADM as soon as they suffer a relapse/recurrence, or when withdrawal proves to be unfeasible.

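### Trial 2: the per-protocol analysis has no stated weight in the non-inferiority decision, so incomplete withdrawal can favour a claim about stopping medication

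*Protocol article*

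**What the plan says.** Under Primary analyses, one statement covers the superiority trial (trial 1) and the non-inferiority trial (trial 2): "Our primary analyses will be based on intention-to-treat. Subsequently per-protocol analyses will be conducted". The same section gives trial 2 a single rule, based on a one-sided confidence interval: "if a difference of 25% can be excluded, then we will conclude non-inferiority of MBCT in comparison with mADM". The rule names no analysis set. Intention-to-treat applies because it is the one called primary, and nothing says what follows if the per-protocol result differs.

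The section on the MBCT arm with tapering asks patients to taper from session 7 of the course and adds: "Patients are reassured that they can restart ADM as soon as they suffer a relapse/recurrence, or when withdrawal proves to be unfeasible". The Background says that adherence to maintenance medication is typically low, without giving a rate.

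Trial 2's question is put in two ways. The Aims and Design sections compare regimens: MBCT with a tapering scheme against MBCT with continued medication. The abstract asks "how large is the risk of relapse/recurrence in patients withdrawing from mADM after participating in MBCT", compared with patients who go on using it. The Discussion likewise speaks of the effect of discontinuing antidepressants after MBCT.

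**The concern.** In a superiority trial, non-adherence usually narrows the intention-to-treat difference and makes a positive claim harder. In a non-inferiority trial the same narrowing makes the claim easier. The article applies one hierarchy to both designs.

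Three kinds of departure bring trial 2's arms together on the primary outcome:

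- taper-arm patients who never stop;
- taper-arm patients who restart before any relapse because withdrawal is unfeasible;
- combination-arm patients who stop on their own.

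Restarting after a relapse is different. The outcome is any relapse or recurrence in 15 months, so that event is already counted and the restart dilutes nothing.

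At stake is the meaning of a positive result. Patients and clinicians could read it as evidence that stopping medication after MBCT is acceptable, when part of the small difference arose because some patients did not stop.

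**Working it through.** **Inputs from the article.** Trial 2 has 140 per group, one-sided alpha 0.05 and a margin of 25 percentage points (Sample size, Trial 2). For the combination arm, "we expect an even lower relapse/recurrence percentage (about 35%) in the combination group" (Sample size, Trial 1).

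**Assumed inputs.** The true effect of withdrawal lies exactly on the margin, so patients who withdraw relapse at 35% + 25% = 60%. A share q of the taper arm does not withdraw and has relapse risk r. The article gives neither q nor r. I take q = 10%, 20% and 30%, with r = 35% (the full combination-arm risk) or r = 50% (patients who cannot withdraw are at higher risk).

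**Formula.** The taper-arm rate under intention-to-treat is

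p_T = 0.60(1 − q) + r·q, with p_C = 0.35.

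Non-inferiority is declared if p̂_T − p̂_C + 1.645·SE < 0.25. To a normal approximation the probability of this is

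Φ[(0.25 − (p_T − p_C))/SE − 1.645], with SE = √{[p_C(1 − p_C) + p_T(1 − p_T)]/140}.

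**The plan's own level first.** At q = 0 the difference is 0.25 and the probability is Φ(−1.645) = 5.0%. Exact binomial enumeration gives 4.8%. The nominal level holds when everyone withdraws.

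**Worked case, q = 20%.**

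- r = 35%: p_T = 0.48 + 0.07 = 0.55, difference 0.20, SE = √(0.475/140) = 0.0582. Φ(0.05/0.0582 − 1.645) = Φ(−0.79) ≈ 21.6%; exact 21.2%.
- r = 50%: p_T = 0.48 + 0.10 = 0.58, difference 0.23, SE = 0.0580. Φ(0.02/0.0580 − 1.645) = Φ(−1.30) ≈ 9.7%; exact 9.4%.

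**Exact probability of declaring non-inferiority under intention-to-treat:**

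| q | p_T if r = 35% | Probability | p_T if r = 50% | Probability |
|---|---|---|---|---|
| 0% | 0.600 | 4.8% | 0.600 | 4.8% |
| 10% | 0.575 | 11.0% | 0.590 | 6.9% |
| 20% | 0.550 | 21.2% | 0.580 | 9.4% |
| 30% | 0.525 | 35.6% | 0.570 | 12.7% |

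Departure in both arms adds up. If 10% of each arm takes on the other arm's risk, then p_T = 0.575, p_C = 0.375, the difference is 0.20 and the probability is about 21%.

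**Requiring both analyses.** Suppose non-withdrawal is unrelated to prognosis and r = 35%. Simulation with 200,000 replicates gives a joint false-claim rate of 4.8%, 4.8% and 4.9% at q = 10%, 20% and 30%. With true rates of 35% in both arms, power falls from 99.7% for intention-to-treat alone to 99.5%, 99.3% and 99.0%.

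**Where that protection weakens.** Suppose the whole taper arm would relapse at 60% if withdrawn, but the excluded non-withdrawers would have relapsed at 80%. The per-protocol taper rate is then (0.60 − 0.80q)/(1 − q) = 57.8%, 55.0% and 51.4%, with 126, 112 and 98 patients. The per-protocol analysis alone then passes with probability about 10%, 20% and 38%.

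**Sample size.** The stated 140 per group does not follow from a 25-point margin at equal rates of 35%: 2(0.35)(0.65)(1.645 + 0.842)²/0.25² rounds up to 46. That is a separate matter. I use 140 because it is what the plan fixes; with fewer patients the inflation is smaller (at 45 per group, q = 20% and r = 35%, it is 12%).

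**The case against.** The strongest reply is that the Aims section asks about regimens, and that restarting when withdrawal is unfeasible belongs to the taper regimen. For that question intention-to-treat is the right analysis and its 5% level is intact. This stands. A reader might infer that intention-to-treat is the wrong primary analysis, or that trial 2's error rate is simply inflated. The documents do not support either; the inflation concerns only the withdrawal question in the abstract and discussion.

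Second, per-protocol analyses are planned, under the heading for primary analyses, and the decision sentence names no analysis set. The detailed definition of the per-protocol set may properly sit in a fuller document. This also stands. What remains is that the article itself ranks the two analyses and states the decision rule, and does so identically for a superiority and a non-inferiority trial.

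Third, a reader might infer that any restart of medication dilutes the comparison, since the article allows it. Only restart before relapse does.

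Fourth, 36% could be taken as the expected error rate. It needs a true effect exactly on the margin, 30% non-withdrawal and non-withdrawers with the full 35% risk. None of these is stated as an expectation for trial 2, and at 50% risk the figure is 13%.

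Finally, a per-protocol set is chosen by behaviour after randomisation and can be biased in either direction. That is a reason to require both analyses and not to substitute one for the other.

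**Conclusion.** The point holds in a limited form. The article makes intention-to-treat primary in both trials and gives the per-protocol result no stated part in trial 2's conclusion. A positive result would support the regimen of offering a taper at the 5% level. It would not, at that level, support a statement about actually withdrawing, and the article poses that question too.

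The excess depends on an unstated share of non-withdrawers and on their risk. Over the assumed range of 10% to 30%, the false-claim probability at the margin is 11% to 36% if their risk is 35%, and 7% to 13% if it is 50%. The direction is foreseeable from the article's own remarks on restarting and on low adherence; the size is not known. This is a worthwhile and inexpensive correction, and it does not invalidate the trial.

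**What to change.** For trial 2, add to the decision rule: non-inferiority of withdrawal is concluded only if the one-sided upper limit excludes the margin in both the intention-to-treat and the per-protocol analysis. If only intention-to-treat excludes it, the conclusion is limited to the regimen of offering a taper after MBCT.

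Fix the per-protocol set before the data are examined, from session attendance, the daily calendar and the MMAS, all of which are already collected. The threshold of at least 4 of 8 sessions, already used for the mediation analyses, could serve for attendance. Judge medication status only up to the first relapse, so that a patient who withdraws, relapses and then restarts stays in the set with the event counted. Adjust this analysis for the baseline minimisation factors. Trial 1 stays as intention-to-treat.

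The cost is a short addition to the text and the definition of a set for an analysis already planned. The joint rule can never be more permissive than intention-to-treat alone, and at equal 35% rates it loses under one percentage point of power for q up to 30%. Its limit should be stated beside it: selection after randomisation means that it protects only partly when non-withdrawal is related to prognosis.

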### Interventions

#### mADM

All study participants are on a stable dose of mADM for at least 6 months prior to enrollment (inclusion criterion). In the mADM group participants continue their use of mADM during the study period of 15 months. After randomization, participants are seen by a study psychiatrist for a review of their mADM. For optimization of mADM, psychiatrists taking part in the study use a protocol based on national [32] and international [33] guidelines, made applicable for the MOMENT study by two experts in pharmacological treatment of MDD ([name]). Switching or augmenting medication is allowed between T0 and T1, and recommendations to manage side effects are provided. Compliance with mADM is measured prospectively during the whole study period using a daily calendar. Participants in the mADM condition are invited to take part in the MBCT training after the study period if they are interested.

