#### mADM + MBCT

In the combination group participants are seen by a psychiatrist for a review of their mADM as described above, and are asked to continue their mADM during the study period. In addition, these patients are invited to take part in the MBCT training, a manualized group skills-training program [11]. MBCT is based on the protocol of Mindfulness-Based Stress Reduction (MBSR) which was developed by Jon Kabat-Zinn [34] combined with elements of Cognitive Behavioral Therapy (CBT [35]), turning it into a relapse prevention programme for patients with recurrent depression. The training consists of eight weekly sessions in a group (8 – 15 participants) with a duration of 2.5 hours, plus one day of silent practice between the 6th and 7th session. The silent day, although originally not in the MBCT program, was incorporated following the MBSR protocol [34] to give participants the opportunity to deepen their mindfulness practice. Formal meditation exercises that are part of the program are the body scan, sitting meditation, walking meditation and mindful movement. The program also encourages participants to cultivate awareness of everyday activities, such as eating or taking a shower. Cognitive techniques that are part of the program are education, monitoring and scheduling of activities, identification of negative automatic thoughts and devising a relapse prevention plan. Participants are expected to practice meditation at home for about an hour a day. In addition, participants in the MBCT conditions are invited to take part in three booster sessions every three months during the study period (around 3, 6 and 9 months after MBCT) to enhance their mindfulness practice through peer and teacher support and rehearsal of the key components of MBCT. *Delivery of MBCT and check for competence and adherence.* MBCT courses are provided at 12 different locations in the Netherlands and are led by one or two MBCT teachers per site. MBCT teachers were trained in the study protocol for MBCT during a 3-day training retreat in the beginning of the project, as well as at three subsequent training days every 6 months. Teaching sessions of each (pair of) teacher(s) are videotaped to check treatment integrity. Two tapes per teacher are randomly selected and rated by highly experienced MBCT/MBSR trainers. Competence and adherence are evaluated with the Mindfulness-Based Interventions – Teaching Assessment Criteria [36].

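### Trial 1 gives MBCT in groups to one arm only, yet its sample size and Chi-square test assume independent patients; any correlation within course or teacher raises the type I error and lowers valid power, probably modestly

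*Protocol article*

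**What the plan says.** **Delivery.** The Interventions section describes two different modes of treatment in trial 1. For the control arm, "In the mADM group participants continue their use of mADM during the study period of 15 months", with a psychiatrist's medication review and MBCT offered only after the study. For the other arm, "The training consists of eight weekly sessions in a group (8 – 15 participants) with a duration of 2.5 hours", and "MBCT courses are provided at 12 different locations in the Netherlands and are led by one or two MBCT teachers per site". Group booster sessions follow.

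**Sample size, Trial 1.** "For trial 1 we need to recruit 96 participants (n = 48 per group"), to detect the difference "with a power of 80% (alpha 0.05, one-sided"). The rates are given as follows: "Our expected difference is therefore 60% (mADM) minus 35% (mADM + MBCT) resulting in 25" percentage points. No ICC or design effect enters.

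**Primary analyses, Trial 1.** "Relapse/recurrence rates will be compared with a Chi-square test". All analyses are to be run with and without covariates, research centre among them, and Randomization also minimises on centre. Multilevel methods appear only under Mechanisms of change, for the session-by-session attention and affect data, not for relapse.

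**Not stated.** The article does not give an ICC, the number of trial 1 patients in a course, or whether courses also held trial 2 patients.

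**The concern.** Patients are randomised individually, but those allocated to mADM + MBCT then share a course, a teacher and booster sessions. Their outcomes may therefore be correlated, while mADM patients have no such grouping. This is a partially nested design.

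A positive correlation inflates the variance of the relapse rate in the MBCT arm only. The Chi-square test ignores that, so its standard error would be too small. Two things are at stake:

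- the false-positive rate of the test that carries trial 1's superiority conclusion;
- the 80% power, which would hold only for a test that ignores the grouping.

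A favourable run of courses, or one particularly good teacher, could then be read as a general effect of MBCT.

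**Working it through.** **Inputs from the article:** relapse 60% and 35%; 48 per arm; one-sided alpha 0.05; power 80%; 12 locations; courses of 8 to 15 attendees; 280 patients in trial 2, all of whom attend MBCT. **Assumed, because not given:** the ICC, and m, the number of trial 1 patients per cluster.

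**1. The plan's own figure.** The mean rate is 0.475.
- Pooled formula: n = [1.645·√(2·0.475·0.525) + 0.842·√(0.60·0.40 + 0.35·0.65)]² / 0.25² = 48.3 per arm (49 rounded up).
- Unpooled formula: (1.645 + 0.842)²·0.4675 / 0.0625 = 46.2 (47 rounded up).
- Power at 48 per arm, pooled: 79.8%.

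So 48 is the plain independence calculation, with no reserve for a design effect.

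**2. A plausible m.** The 48 MBCT-arm patients over 12 locations average 48/12 = 4 per location. With one or two teachers at each, that is about 2 to 4 per teacher. If trial 2 patients share courses, (48 + 280) = 328 patients in groups of 8 to 15 make 22 to 41 courses, or 48/41 = 1.2 to 48/22 = 2.2 trial 1 patients per course.

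**3. Formulas.** The design effect, DE = 1 + (m − 1)·ICC, applies to the MBCT arm only.
- Type I error of the unadjusted test, one-sided: 1 − Φ(1.645 / √((1 + DE)/2)).
- Power of a correctly sized test: Φ((0.25 − 1.645·SE0) / SE1), with SE0 = √(0.475·0.525·(1 + DE)/48) and SE1 = √((0.24 + DE·0.2275)/48).

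Example, m = 4 and ICC 0.05: DE = 1.15, SE0 = 0.1057, SE1 = 0.1022. Alpha = 1 − Φ(1.645/1.037) = 0.056. Power = Φ((0.25 − 0.1738)/0.1022) = Φ(0.745) = 77.2%.

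**4. Results, 48 per arm.**

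| m | ICC | DE | One-sided alpha, unadjusted test | Power, correctly sized test |
|---|---|---|---|---|
| any | 0 | 1.00 | 0.050 | 79.8% |
| 2 | 0.02 | 1.02 | 0.051 | 79.4% |
| 2 | 0.05 | 1.05 | 0.052 | 78.9% |
| 2 | 0.10 | 1.10 | 0.054 | 78.0% |
| 4 | 0.02 | 1.06 | 0.053 | 78.7% |
| 4 | 0.05 | 1.15 | 0.056 | 77.2% |
| 4 | 0.10 | 1.30 | 0.063 | 74.7% |
| 8 | 0.05 | 1.35 | 0.065 | 73.9% |
| 15 | 0.05 | 1.70 | 0.078 | 68.5% |

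If the Chi-square test is read two-sided at 0.05, its size for m of 2 to 4 and ICC 0.02 to 0.05 is 0.051 to 0.059.

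**5. Simulation.** A beta-binomial simulation of the unadjusted test (200,000 replicates, 60% in both arms, m = 4) gave a one-sided size of 5.5% with independent data, 5.9% at ICC 0.02, 6.1% at 0.05 and 6.7% at 0.10. The baseline above 5% reflects the discreteness of the test. The increments of 0.4, 0.7 and 1.3 points are close to the formula's 0.3, 0.6 and 1.3.

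**6. Uneven recruitment.** With a mean of 4 and an assumed coefficient of variation of 0.7, the effective m is 4·(1 + 0.49) = 5.96. At ICC 0.05, DE = 1 + 4.96·0.05 = 1.248, alpha is 0.060 and valid power is Φ((0.25 − 0.1778)/0.1045) = 75.5%.

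**The case against.** **Cluster size.** A reader might take the stated course size of 8 to 15 as the cluster size and infer that valid power falls to between 74% and 69% at ICC 0.05. The article does not support this. That range is total attendance. Filling whole courses with trial 1 patients would mean 48/15 to 48/8, or three to six courses in the entire trial, which sits badly with 12 locations. This objection stands, and it brings the effect down to the m = 2 to 4 rows. It does not remove it: patients in successive courses at a site can share a teacher, so mixing in trial 2 patients need not shrink the teacher-level cluster.

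**An unconditional claim.** A reader might also infer that the false-positive rate is known to be too high. It is not. With ICC 0 nothing is distorted. If MBCT changed no patient's outcome at all, the randomised comparison would stay valid despite the grouping. Inflation requires courses or teachers that differ in effect while averaging zero. This also stands, so the point is conditional.

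**Centre balance.** Minimisation on centre balances centre differences between the arms, which makes an unadjusted test conservative with respect to them. In a simulation with 12 centres and 4 patients per arm in each, a shared centre ICC of 0.05 plus an MBCT-only group ICC of 0.05 gave a one-sided size of 0.049 (m = 2) to 0.054 (m = 4). With centre ICC 0.02 it was 0.050 to 0.057. The offset is real, but its size rests on another assumed ICC. A centre term shared by both arms still does not model variation that exists in one arm only.

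**Left to the analysis plan.** A clustering sensitivity analysis may be specified in a plan that is not shown. But the article itself names the primary test, and that test assumes independence.

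**Conclusion.** The point holds in conditional form. Trial 1 is partially nested, and both its sample size and its named primary test treat patients as independent. For any positive ICC with two or more trial 1 patients per cluster, and leaving aside the offset from centre balance, the unadjusted test's type I error is above nominal and the power of a correctly sized test is below the figure stated.

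The likely size is modest. Under the m and ICC ranges taken as most plausible above (2 to 4 and 0.02 to 0.05), valid power is about 0.4 to 2.6 points lower than under independence. It is about 5 points lower at m = 4 and ICC 0.10, and about 4 points lower at ICC 0.05 with the uneven recruitment assumed above. These figures rest on assumed ICCs and an inferred cluster size. The matter is worth correcting because the calculation has no margin and the correction is cheap, not because the trial 1 conclusion is shown to be unsafe.

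**What to change.** - **Data:** record the MBCT course and teacher for each patient.
- **Primary analyses, Trial 1:** estimate the risk difference with a variance that clusters by course or teacher in the mADM + MBCT arm, counting each mADM patient as a cluster of one, with a small-sample correction because clusters are few. Report the plain Chi-square test alongside. A robust variance suits clusters this small better than a mixed model, which would estimate the group variance poorly.
- **Sample size, Trial 1:** keep 96 patients, say that the 80% assumes no clustering, and give power over a range of assumed ICCs with about 2 to 4 trial 1 patients per cluster. The results above give 79.4% to 78.7% at ICC 0.02, 78.9% to 77.2% at 0.05 and 78.0% to 74.7% at 0.10.

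Trial 2 needs no change on this account, since both its arms attend MBCT.

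**Cost:** one or two recorded variables and some analysis wording, with no extra patients. The confidence interval would be slightly wider (at m = 4 and ICC 0.05, SE1 is 0.1022 against 0.0987 under independence, about 4%), and the stated power slightly less favourable.
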